**Missed**													
**Follow-up**						*****	*****	*****	*****	*****	*****	*****	
**Early W/D**						*****	*****	*****	*****	*****	*****	*****	*****

*****Complete forms when and/or if applicable.

**Figure 2 F2:**
[figure not shown]
**Limiting loss to follow-up; Reference: Sprague S, Leece P, Bhandari M, Tornetta P, Schemitsch E, Swiontkowski M, SPRINT Investigators.** Limiting loss to follow up in a multicentre randomized controlled trial in orthopaedic surgery. Controlled Clinical Trials. 2003;24:719–725.

### Protecting against sources of bias

#### *Blinding*

In the FAITH trial surgeons cannot be blinded since the implants for the two treatment arms are easily distinguishable. Patients cannot be blinded because resulting surgical scarring patterns from both fixation procedures indicate which treatment was performed. Additionally, some patients and/or their caregivers often wish to review x-rays during clinic follow-up visits. Outcome assessors cannot be blinded as blinded images create difficulty in accurately adjudicating patient eligibility, radiographic characteristics, surgical quality, healing, and study events. Data analysts will be blinded.

#### *Surgeon expertise*

Similarly to other trials that evaluate two or more surgical interventions, there is a risk of differential expertise bias [37]. However, training in both methods of internal fixation examined in FAITH are standard training for Orthopaedic surgeons. We will also recommend that surgeons participating in the FAITH trial should meet 2 criteria for expertise for either cancellous screw fixation or sliding hip screw fixation: (1) Surgeons should have performed at least 25 procedures (of either sliding hip screws and/or cancellous screws) in their career (including residency experience in which they assumed responsibility for the procedure); and (2) Surgeons should continue to perform the procedure (at least 5 per year of either sliding hip screws and/or cancellous screws) in the year prior to the trial start date. Additionally, we will standardize aspects of the peri-operative care in order to limit any potential expertise bias and differential use of interventions. With these two procedures in place it is unlikely that a significant degree of expertise bias will be introduced into the trial.

### Maximizing patient retention

Previous trials in hip fracture surgery have lost up to 50% of patients to follow-up [16]. To avoid this problem we will implement several procedures, as outlined in (Figure 2). We have previously used the majority of these strategies to maximize follow-up in multi-centre studies. Key tactics include: (1) Excluding individuals who are likely to present problems with follow-up; (2) Prior to hospital discharge, as well as their own telephone number, each patient will provide the name and address of alternate contacts who are likely to be aware of the patient’s whereabouts; (3) Patients will receive a reminder card for their next follow-up visit from the clinical research coordinator; and (4) Follow-up visits will coincide with standard fracture clinic visits. Alternatively, patients can complete some study visits over the phone for the visits where no radiographs are required. Additionally, we will not withdraw patients if the study protocol was not adhered to (e.g. patient received wrong treatment arm, occurrence of protocol deviations, missed follow-up visits, etc.).

### Minimizing co-intervention and contamination

Any patients who crossover will be analyzed in the group to which they were allocated, maintaining the intention to treat approach for the analysis. It remains possible that surgeons may initially plan upon internal fixation but decide intra-operatively to replace the hip with some form of arthroplasty (i.e., hemi-arthroplasty or total arthroplasty). These patients, who never receive either internal fixation implant, will be excluded from the analysis if the decision to choose arthroplasty could not have plausibly been related to the group to which the patient was randomized. This decision will be made by the CAC. In previous trials of internal fixation versus arthroplasty, 14% of patients randomized to internal fixation implants actually received an arthroplasty [38]. The intraoperative switch to arthroplasty procedures when internal fixation is planned is related to surgeon biases for a particular procedure and the inability to obtain a satisfactory reduction of the femoral fracture for the placement of internal fixation.

Our standardization of management protocols will limit co-interventions, and we will document the use of drugs that affect the bone, and major additional procedures that patients undergo. Similarly, the use of medications that affect bone metabolism will be discouraged, but not prohibited. Research coordinators will record all medications such as a bisphosphonates, hormone replacement therapy, selective estrogen receptor modulators, calcitonin, and anabolic steroid therapy used concurrently.

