### Study outcomes

#### *Primary study endpoints*

The primary study endpoint is re-operation within 24 months post initial surgery to promote fracture healing, relieve pain, treat infection, or improve function including the following: (1) Implant removal prior to fracture healing; (2) Revision surgery with another internal fixation implant; (3) Revision surgery to arthroplasty; and (4) Soft tissue procedures, especially incision and drainage for deep infection at the bone implant interface. Classification of the reason for revision surgery is as follows: (1) Implant failure (2) Superficial or deep infection ; (3) Avascular necrosis; (4) Hip instability; (5) Hip dislocation; (6) Open wound; (7) Painful hardware; (8) Intractable pain due to wear of the acetabulum; (9) Peri-prosthetic femur fracture; and (10) Nonunion. Other classifications will be used if applicable. Planned revision surgeries will not be considered study events (i.e., technical malreduction requiring early revision). Criteria for the diagnosis of nonunion will include a failure of the fracture to progress towards healing for at least 2 months on consecutive radiographs. This will be evident as a persistent fracture line on radiograph, continued pain with hip range of motion, and the inability to weight-bear without pain. Avascular necrosis will be defined as a process that is characterized pathologically by bone marrow ischemia and eventual death of trabecular bone. Infection will be classified according to the Center for Disease Control Criteria [29].

Our choice of a 24 month follow-up period is dictated by the following 2 factors: (1) We have established a consensus among participating surgeons that the decision to re-operate on the hip fracture would occur within the first 24 months following surgery in all, or virtually all, patients and (2) Previous studies have reported 100% of revision surgeries occurring between 2 and 12 months for undisplaced fractures and 70-100% in 24 months for displaced fractures. Although nonunion and avascular necrosis may be present after 24 months, previous studies suggest that 70-98% of revisions due to nonunion and avascular necrosis occur within 24 months [30,31]. Thus, we can expect that nearly all the revision surgeries will occur within 24 months.

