### Adjudication of study events

The CAC is comprised of a Chairperson plus three orthopaedic surgeon committee members. The CAC is responsible for assessing patient eligibility (if in doubt) and they will independently adjudicate radiographic characteristics and quality of the surgery, fracture healing, revision surgeries, fracture-related complications (i.e., avascular necrosis, nonunion, malunion, implant breakage or failure, infection), and mortality. The adjudicators may review the patients’ case report forms and x-rays and determine if the reported outcome meets the criteria for being a study event. Any disagreements between the adjudicators will be discussed and resolved during consensus conference calls with the CAC. If consensus cannot be reached after extensive discussion, a vote will be permitted at the discretion of the Chair. All decisions made by the committee will be final. The CAC members will not be blinded to treatment as it is not possible to accurately judge blinded images; however, they will be blinded to the name and location of the clinical site.

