### Statistical methods

#### *Primary analysis*

All outcome analyses will adhere to the intention to treat principle. To evaluate the effect of sliding hip screw versus cancellous screws in time to revision rates, a Cox proportional hazards model will be used with the following covariates that are included in the minimization procedure: (1) Age (50–80 years or >80 years (81 years or older)); (2) Undisplaced or displaced femoral neck fractures; (3) Pre-fracture living setting (i.e., institutionalized or not institutionalized); (4) Pre-fracture functional status (i.e., using ambulatory aid or independent ambulator); (5) American Society for Anesthesiologists (ASA) Class (i.e., Class I/II or III/IV/V); and (6) Clinical site.

The treatment effect will be evaluated using a likelihood ratio test, and the validity of the proportional hazards assumption of the Cox model will be assessed. Survival rates at each follow-up period will be compared and then the overall difference between survival curves with log-rank tests will be evaluated, adjusting for the covariates. Absolute revision rates, risk reduction, absolute risk reduction, and the number needed to treat with screws and sideplate will be calculated. All results will be presented with 95% confidence intervals.

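### The protocol promises intention to treat, yet removes some randomised patients switched intra-operatively to arthroplasty on the judgement of a committee that knows the allocation

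*Protocol article*

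**What the plan says.** Protocol article, Primary analysis: "All outcome analyses will adhere to the intention to treat principle".

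Minimizing co-intervention and contamination opens in the same spirit: "Any patients who crossover will be analyzed in the group to which they were allocated, maintaining the intention to treat approach". It then treats one group differently. Patients who receive neither fixation implant because the surgeon changes to arthroplasty during the operation "will be excluded from the analysis if the decision to choose arthroplasty could not have plausibly been related to the group" of randomisation. On who decides: "This decision will be made by the CAC". The same paragraph gives two causes for such switches, namely surgeon bias towards a procedure and failure to reach a satisfactory reduction. It reports that in earlier trials of fixation against arthroplasty "14% of patients randomized to internal fixation implants actually received an arthroplasty".

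On blinding, Adjudication of study events says: "The CAC members will not be blinded to treatment as it is not possible to accurately judge blinded images". Members are blinded only to the name and location of the site. The Blinding section agrees ("Outcome assessors cannot be blinded as blinded images create difficulty in accurately adjudicating patient eligibility") and adds that surgeons cannot be blinded. Study follow-up and Maximizing patient retention both say that patients are not withdrawn for departures from protocol.

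**The concern.** Intention to treat protects the comparison because membership of the analysis set is fixed at randomisation. Here membership for some patients is fixed later. It turns on a decision by a surgeon who knows the arm, followed by a ruling from a committee that also knows the arm. The only criterion shown is plausibility.

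If switches are made, or judged unrelated, more readily in one arm, the two analysed groups are no longer the randomised groups. Blinding the data analysts does not help, because the exclusion is made before the data reach them. The article defines no other primary set and shows no all-randomised analysis beside this one, so *the analysis* is fairly read as including the primary comparison. What is at stake is the validity of the primary treatment estimate.

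**Working it through.** **1. The texts side by side**

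| Question | What the protocol gives | Section |
|---|---|---|
| Who is analysed? | Everyone, as allocated | Primary analysis |
| Switched to the other implant? | Kept, as allocated | Minimizing co-intervention |
| Switched to arthroplasty, possibly related to allocation? | Kept | Minimizing co-intervention |
| Switched to arthroplasty, judged unrelated? | Excluded | Minimizing co-intervention |
| Does the surgeon know the arm? | Yes | Blinding |
| Does the committee know the arm? | Yes | Adjudication of study events |

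The fourth row cannot stand with the first.

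**2. Could the switch depend on the implant?** The protocol's own facts allow it. Its surgeon survey found that 90% preferred cancellous screws for undisplaced fractures, as did 68% of those choosing fixation for displaced ones. The Surgeon expertise criteria may be met with either implant, so a surgeon can be assigned the less familiar one. None of this shows that switching differs by arm, but it means that independence cannot be assumed.

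**3. Size of a possible bias.** Assume no true effect. Let one arm lose a further fraction x of its patients, and let r be their re-operation risk relative to the arm average. Neither x nor r is given for this trial.

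Apparent risk ratio = (1 − r·x) / (1 − x)

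| x | r = 2 | r = 0.23 |
|---|---|---|
| 3% | 0.94/0.97 = 0.97 | 0.9931/0.97 = 1.02 |
| 5% | 0.90/0.95 = 0.95 | 0.9885/0.95 = 1.04 |
| 7% | 0.86/0.93 = 0.92 | 0.9839/0.93 = 1.06 |

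r = 2 stands for patients whose fractures are hard to reduce and who stay at high risk. r = 0.23 borrows the risk ratio for revision, arthroplasty against fixation in displaced fractures, from Inconclusive clinical evidence. Both are illustrations.

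**4. Power: exclusion against retention.** Table 3 gives 86.3% power at a 30% relative risk reduction and N = 1,000. Taking the hazard ratio as 0.70 and using Schoenfeld's formula, events = 4(1.960 + 1.094)² / (ln 0.70)² = 293. Conversely, Φ(√293/2 × 0.3567 − 1.960) = 86.3%. The 293 is thus back-solved, because the article prints no event count for Table 3. A two-year model on the stated event, mortality and loss rates gives 86.4% without crossover dilution and 81.2% with 3.4% crossover per arm, so this base is itself approximate.

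Let a share s switch in each arm, with the same risk after arthroplasty in both arms, equal to the control-arm average. Control-arm events are 293/1.70 = 172.4.

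- Exclude all switched patients: events = 293(1 − s), hazard ratio 0.70.
- Keep them all: hazard ratio = 0.70(1 − s) + s, and events = 172.4 × (1 + that ratio).

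| s | Exclude all | Keep all |
|---|---|---|
| 2% | 85.6% (287 events) | 84.7% (HR 0.706, 294 events) |
| 5% | 84.5% (278 events) | 82.2% (HR 0.715, 296 events) |
| 14% | 80.8% (252 events) | 73.4% (HR 0.742, 300 events) |

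At s = 14%, retention gives 79% if switched patients have 0.23 times the average risk and 67% if they have twice it. Retention has the lower power in every row.

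**The case against.** The rule is narrower than a quick reading suggests. A reader might infer that all patients switched to arthroplasty are dropped. They are not: the default is retention, and only switches judged not plausibly related to allocation go. Excluding patients whose switch truly had nothing to do with allocation would not bias the comparison in expectation. If surgeon bias and failed reduction may always depend on the implant, a strict committee would exclude almost nobody.

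That stands as far as it goes. It also means that the rule is either idle, in which case removing it costs nothing, or active, in which case it rests on unblinded case-by-case judgement.

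Three further inferences do not hold:

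- *About 140 of 1,000 patients would be lost.* The 14% comes from trials in which arthroplasty was the competing arm. In FAITH both arms are fixation, and no switch rate is given. Applying 14% and excluding every case is an upper illustration only.
- *The rule would manufacture a benefit.* The apparent ratio falls on either side of 1, depending on the risk of the excluded patients after arthroplasty.
- *The rule costs power that the fix would restore.* Against a trial with no switching, exclusion does lose power. Against the actual alternative of keeping switched patients, it does not.

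A reader might also attach the endpoint rule "Planned revision surgeries will not be considered study events (i.e., technical malreduction requiring early revision") to this point. That rule defines events and removes no patient, so it does not breach intention to treat. Nothing in the article shows that it acts differently by implant. It is a separate question.

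**Conclusion.** The point holds as a contradiction in the text with a real, unquantified threat to validity. The protocol states intention to treat without exception and then fixes an exception that depends on an event after randomisation, assessed by people who know the arm. Differential exclusion cannot be ruled out; the documents do not show that it would occur.

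For scale, and only under the assumptions above, an excess exclusion of 3% to 7% in one arm moves a null risk ratio to between 0.92 and 1.06. The protocol plans around relative reductions of 25% to 30%, so a shift of this order would not create an effect of the planned size by itself. It could blur or tip a modest one. An analysis plan not shown here may add an all-randomised analysis, but the rule as the article words it still needs correcting.

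**What to change.** In Minimizing co-intervention and contamination, remove the exclusion from the primary analysis. State that every randomised patient is analysed in the allocated arm, whichever implant or prosthesis was used, and that qualifying re-operations after the index operation count. Because parts of the endpoint are worded for fixation implants, add a sentence on how they apply when the index operation was an arthroplasty. The listed reasons for revision already include infection, dislocation and peri-prosthetic fracture.

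Keep the committee-defined exclusion as a labelled sensitivity analysis, with criteria written in advance and preferably decided without sight of the allocation. Report the number switched and the number excluded by arm.

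The cost is wording. These patients are already under follow-up and their re-operations are already adjudicated. The statistical price is dilution: in the average-risk illustration, about 1 point of power at 2% switching (85.6% to 84.7%), about 2 at 5% (84.5% to 82.2%) and about 7 at 14% (80.8% to 73.4%). That price buys a primary comparison of the groups as randomised.

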### Statistical plan

#### *Sample size determination*

The determination of sample size is based upon a comparison for the primary outcome (revision surgery) of the sliding hip screw versus multiple cancellous screw groups. All statistical hypotheses will be assessed using 2-sided significance tests. Alpha levels of 0.05 have been chosen for the primary and 0.01 for the secondary outcomes. Previous studies have reported revision surgery rates in hip fracture patients that have ranged from 0-44% [39-41], with a weighted pooled risk of 22.7% (95% CI: 19.6-25.8%). In a pooled estimate of 5 RCTs comparing sliding hip screw fixation with multiple screw fixation in patients with displaced or undisplaced hip fractures, sliding hip screws reduced the risk of revision by 32% (95% CI: 3-53%, p = 0.04, Q = 5.3) [22,42-45]. The sample size calculation reflects the proposed primary analysis, which will use the Cox proportional hazards model, and is based on methods described by Collett [46]. The goal is to calculate the required number of patients that will yield a sufficient number of outcome events (revision surgeries) in order to have adequate statistical power for a given size of treatment effect. This was done by taking into account the anticipated revision surgery rates in the multiple cancellous screw group, the postulated relative risk reduction with sliding hip screws, and the rates of mortality and loss to follow-up. Because some of these inputs are expected to change over the two year period of follow-up, the expected number of person-years of follow-up and the expected numbers of study events in each group were calculated initially for the first year of follow-up (year 1). The calculations were then repeated for the second year of follow-up (year 2), after having estimated the number of patients in each group who would survive, be event-free, and available for continued follow-up at 12 months post-randomization.

The relative risk reduction was estimated to be 25% [43]. The decision to use a 25% annual event rate in the cancellous screws group for year 1 was based upon the previous literature [25,47] and compelling preliminary aggregate data (blinded to allocation) from our pilot study. Informed by the pilot study, annual mortality rates of 15% and losses to follow-up of 5% were assumed for each group. The annual event rates by group were converted into equivalent hazard rates, assuming for simplicity that the hazard rate would be approximately constant over year 1. It was calculated that approximately 58% and 63% of the group receiving cancellous screws and the group receiving sliding hip screw fixation would be event-free and available for further follow-up at the start of year 2. It was assumed that the revision rate would fall to one-third of its initial value during year 2 of follow-up (i.e., about 10% in the cancellous screws group), that the annual mortality rate would be 10%, and that there would again be 5% of patients lost to follow-up. The sample size was also increased to allow for an estimated combined 6.8% crossover rate from the assigned to the alternate treatment, based on our pilot data.

These assumptions lead to a required total sample size of 1,441 patients, who will yield an expected number of 353 outcome revisions. For convenience, the target number of patients was rounded to 1,500. Table 2 shows the study power for a sample size of 1,500 patients (750 per group) and a range of possible values for the initial revision rate and the relative risk reduction, on either side of the central assumed values. It demonstrates that with the chosen sample size of 750 per group, there will be a high likelihood of detecting a RRR of 25% or greater across the plausible range of revision surgery rates, and moderate power for slightly lower effect sizes.

**Table 2 T2:** Estimated study power for 750 patients per treatment arm (N = 1500)

**Baseline risk**					
**(Year 1)^**	**Relative risk reduction**				
	**10%**	**15%**	**20%**	**25%**	**30%**
**20%**	15.9%	30.8%	50.5%	70.5%	**86.1%**
**25%**	19.6%	38.7%	61.6%	**81.5%**	**93.5%**
**30%**	23.6%	46.8%	71.7%	**89.3%**	**97.4%**
**35%**	28.2%	55.2%	**80.3%**	**94.5%**	**99.1%**
**40%**	33.3%	63.6%	**87.3%**	**97.5%**	**99.7%**

*Number of patients per treatment arm, alpha = 0.05.

^Year 2 risk is 1/3 that of year 1.

Bold numbers indicate statistical power range for this study.

After 589 patients completed study follow-up, event rates were obtained and used to inform power analyses for a reduced sample size of 1,000 patients. A sample size of 1,000 patients was used in order to obtain a balance between feasibility of completing recruitment within a reasonable timeline and obtaining a sample size that will support plausible hypotheses of treatment effect and baseline event rates. Based on event rates calculated from the first 589 patients who completed the study, a 15.5% annual event rate was used for year 1 and a 27.2% annual event rate was used for year 2. Based on the data from the completed patients, it was assumed that the annual mortality rate would be 11.0% (year 1) and 18.2% (year 2) and that there would be a 12.2% (year 1) and 5.9% (year 2) loss to follow-up. The sample size was again increased to allow for an estimated combined 6.8% crossover rate from the assigned to the alternative treatment. Table 3 shows the study power for a sample size of 1,000 patients (500 per treatment group) and a range of possible values for the initial revision rate and the relative risk reduction, on either side of the central assumed values. It demonstrates that with a sample size of 500 per group, there will be a likelihood of detecting a RRR of 30% or greater across the plausible range of revision surgery rates, and moderate power for slightly lower effect sizes.

**Table 3 T3:** Estimated study power for 500 patients per treatment arm (N = 1,000)

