**Baseline risk**							
**(Year 1)^**	**Relative risk reduction**						
	**10%**	**15%**	**20%**	**25%**	**30%**	**35v**	**40%**
**15.5%**	14.5%	28.5%	48.1%	69.3%	**86.3%**	**95.7%**	**99.2%**

*Number of patients per treatment arm, alpha = 0.05.

^Year 2 risk is 27.2%.

Bold numbers indicate statistical power range for this study.

While the revised assumptions based upon data collected from the first 589 patients to complete follow-up differ from the initial assumptions, the event annual rate of revision surgery of 15.5% in year 1 and 27.2% in year 2 are well within the range of 0-44% that have been previously reported in the literatures [39-41].

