## Discussion

Most of the current literature evaluating the efficacy of internal fixation at treating hip fractures is focused on the comparison between internal fixation and arthroplasty, which does not allow for a direct comparison of different methods of internal fixation. The RCTs that directly evaluate different types of internal fixation have been too small to definitively guide Orthopaedic practices as they lack sufficient power to reliably detect important treatment effects and some contain important methodological limitations [16,25]. FAITH will be the largest trial to date informing the question of the impact of cancellous screws and sliding hip screws on outcomes in patients with femoral neck fractures. With over 1000 patients, FAITH will have adequate power to detect important treatment effects and will help to inform Orthopaedic practice. FAITH will include patients from North America, Europe, Asia, and Australia making results generalizable to several different geographic populations.

Our previous trial evaluating reamed versus non-reamed nailing in over 1,300 patients with tibial shaft fractures (SPRINT) set a new benchmark for the conduct of RCTs in Orthopaedic surgery [50,51]. The FAITH trial expands upon the successful methodology employed in SPRINT and will set the bar higher as we expand our collaboration worldwide and recruit a larger number of patients, while maintaining methodological rigor. Ultimately, this RCT will move Orthopaedic surgical trials one step closer to the standards of global impact RCTs that are currently conducted in cardiovascular medicine and cerebrovascular surgery (e.g. POISE Trial Investigators, 2006; PROTECT Investigators, 2011) [52,53].

Since treatment allocation is concealed there will be no risk of conscious or unconscious selection bias on the part of the researchers, as can occur when it is possible for researchers to predict treatment assignment. Further, minimization will be used to ensure prognostic balance between intervention groups for relevant patient factors. The minimization approach evaluates the marginal distribution of each prognostic variable and then sums over the variables as each patient is assigned to a treatment group. Unlike random permuted block within strata, minimization works toward minimizing the total imbalance for all factors together instead of considering mutually exclusive subgroups [26] which may be considered an additional strength.

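### Table 3's 86.3% power uses year-2 revision and death rates that rise without explanation and may be 24-month cumulative figures, and it reproduces only without the stated crossover allowance

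*Protocol article*

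**What the plan says.** All places are in the protocol article.

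- **Sample size determination, revised calculation.** After 589 patients had completed follow-up, "a 15.5% annual event rate was used for year 1 and a 27.2% annual event rate was used for year 2". For deaths, "it was assumed that the annual mortality rate would be 11.0% (year 1) and 18.2% (year 2"). Loss to follow-up is 12.2% in year 1 and 5.9% in year 2. A 6.8% crossover allowance is said to have been applied again.
- **Table 3** (500 per arm) has one baseline row, 15.5%, with year-2 risk footnoted as 27.2%. Power is 69.3% at a 25% RRR and 86.3% at 30%. The text concludes that "there will be a likelihood of detecting a RRR of 30% or greater across the plausible range of revision surgery rates".
- **Below Table 3** the authors acknowledge that the revised assumptions differ from the initial ones and say that the rates "are well within the range of 0-44% that have been previously reported in the literatures".
- **Sample size determination, initial calculation.** "It was assumed that the revision rate would fall to one-third of its initial value during year 2 of follow-up", and annual mortality was to fall from 15% to 10%. The literature range of 0-44% is introduced there "with a weighted pooled risk of 22.7% (95% CI: 19.6-25.8"%).
- **Primary study endpoints** cites earlier studies in which every revision of an undisplaced fracture fell between 2 and 12 months.
- **Discussion:** "With over 1000 patients, FAITH will have adequate power to detect important treatment effects".

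**The concern.** The revised inputs reverse the time course assumed in the initial calculation. Revision rises from 15.5% to 27.2% instead of falling to one-third, and mortality rises from 11.0% to 18.2% instead of falling. The cited timing for undisplaced fractures points the same way as the initial plan. The only defence is that both revision rates lie within 0-44%. That range is not stated to be annual, and it would admit almost any figure.

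A rise in both pairs is what one would see if 24-month cumulative percentages had been entered in the year-2 position. Year-2 events and deaths would then be over-counted. Table 3 is the only power evidence offered for 1,000 patients, so an error there carries into the claim about a 30% RRR and into the Discussion's statement on power.

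**Working it through.** **Inputs.** Sample size determination: two-sided alpha 0.05; 500 per arm; revision 15.5% / 27.2%; death 11.0% / 18.2%; loss 12.2% / 5.9%; crossover 6.8%. Each annual rate p becomes a hazard -ln(1-p). Revision, death and loss act as competing exits within each year. Power = Φ(½·√D·|ln HR|·k - 1.96), where D is the number of events and k a crossover factor (k = 1 means no allowance).

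**1. Reproducing Table 3 with the rates as annual.**
- Year 1: hazards 0.1684, 0.1165, 0.1301 (sum 0.4151). Fraction leaving = 1 - 0.845×0.890×0.878 = 0.3397. Events per 1,000 = 1,000×0.3397×0.1684/0.4151 = 137.8; 660.3 remain.
- Year 2: hazards 0.3175, 0.2009, 0.0608 (sum 0.5792). Fraction leaving = 1 - 0.728×0.818×0.941 = 0.4396. Events = 660.3×0.4396×0.3175/0.5792 = 159.1.
- Total 297. With HR = 1 - RRR and k = 1:

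| RRR | 10% | 15% | 20% | 25% | 30% | 35% | 40% |
|---|---|---|---|---|---|---|---|
| Table 3 | 14.5 | 28.5 | 48.1 | 69.3 | 86.3 | 95.7 | 99.2 |
| 297 events | 14.6 | 28.8 | 48.5 | 69.8 | 86.7 | 96.0 | 99.3 |

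Back-solving the printed row gives about 293 events. So 27.2% was used as a further annual rate on top of 15.5%.

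**2. What those inputs imply.** 24-month revision risk net of death and loss = 1 - 0.845×0.728 = 38.5%; the crude equivalent is 297/1,000 = 29.7%.

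**3. If the year-2 figures are cumulative.** Conditional year-2 revision = 1 - 0.728/0.845 = 13.8%; death = 1 - 0.818/0.890 = 8.1%. Year-2 hazards are then 0.1490, 0.0844, 0.0608 (sum 0.2942), the fraction leaving is 0.2549, and year-2 events = 660.3×0.2549×0.1490/0.2942 = 85.3. Total 223, a ratio of 223/297 = 0.751.
- On Table 3's scale: D = 293×0.751 = 220; ½·√220×0.3567 = 2.646; Φ(0.686) = 75.4%. The stated figure is 86.3%, so the fall is about 11 points.

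**4. Crossover, using a method that fits Table 2.** Here the RRR is applied to the treated arm's risk, so treated-arm events fall, and HR = ln(1 - 0.155×0.70)/ln(1 - 0.155) = 0.682 (|ln HR| = 0.383). With k = 0.932 (that is, 1 - 0.068) every Table 2 cell is matched within 1.2 points; with k = 0.914, within 1.0 point. At a 30% RRR:

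| | D | k = 1 | k = 0.932 | k = 0.914 |
|---|---|---|---|---|
| Rates as stated (annual) | 255 | 86.4% | 81.3% | 79.8% |
| Year 2 cumulative | 191 | 75.4% | 69.4% | 67.7% |

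The printed 86.3% appears only with k = 1. Like for like, the cumulative reading costs about 12 points with the allowance included.

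**5. If 27.2% is a crude 24-month proportion, already net of death.** Applying death and loss again would discount twice. Events are then 1,000×0.272 = 272 (27.2% in both arms), or 500×0.272 + 500×0.272×0.70 = 231. With HR 0.70, power runs from 83.7% (272 events, no crossover allowance) to 71.5% (231 events, log HR multiplied by 0.932).

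**6. Detectable RRR at 80% power, Table 3's scale.** 1 - exp(-2×2.80/√D) = 28% at 293 events and about 31% at 220.

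**The case against.** The best defence is that Table 3 agrees with its stated inputs. The text calls the rates annual twice, they come from the trial's own patients, and the authors say openly that they differ from the initial assumptions. The sentence that gives mortality also gives loss of 12.2% then 5.9%; that pair falls, so it cannot be cumulative. All of this stands, and it is why a reader should not infer that the cumulative reading is established.

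Nor does 38.5% prove an error. It is a net risk. Its crude equivalent, 29.7%, is close to the roughly 30% revision figure in the Background and the 30.2% for displaced fractures under Subgroup analyses. The initial plan (25%, then about 10%) also compounds to 1 - 0.75×0.90 = 32.5%, above the pooled 22.7%. The 2-to-12-month timing concerns undisplaced fractures only; no year-1/year-2 split is given for displaced fractures, expected to be two-thirds of patients.

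Comparing 86.3% directly with 68% would also mislead, because about 6.5 points of that gap (86.3 - 79.8) come from the crossover and method difference, not from the year-2 rates.

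Finally, the consequence is bounded. The pooled RRR quoted from five trials is 32%, feasibility also drove the choice of 1,000, that number is a minimum, and results will carry 95% confidence intervals. None of this explains why both rates rise in year 2 or why the crossover allowance does not appear in the printed figure.

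**Conclusion.** The point holds in this form: the power behind 1,000 patients rests on year-2 revision and death rates whose meaning is uncertain and whose rise is unexplained, and the printed figure does not reflect the crossover allowance described.

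- Firm: Table 3 treats 27.2% as a second annual rate; 86.3% reproduces only without crossover; with the Table 2 method the stated annual rates give about 80-81%. Table 3's single baseline row cannot show power across a range of revision rates.
- Conditional on a cumulative reading, with death and loss applied on top as the plan does: about 25% fewer events and 11 to 12 points less power at a 30% RRR (86.3% to about 75%, or about 80% to 68% with crossover).
- Conditional on 27.2% being a crude proportion net of death: about 71-84%.

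A reader might go further and conclude that Table 3 contains a proven arithmetical error, or that true power is known to be near 70%. The document does not support either; only the 589-patient data can settle which reading is right.

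**What to change.** From the 589-patient data, pooled over arms so that no comparison is revealed:

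1. State for each year-2 figure (revision, death, loss) whether it is conditional on reaching year 2 or cumulative from surgery, and whether it is crude or net of death and loss.
2. Recompute year-specific hazards as events per person-time at risk.
3. Apply the 6.8% crossover allowance in the same way as for Table 2.
4. Rebuild Table 3 with several baseline-risk rows.
5. Restate the power and the detectable RRR in Sample size determination, in the paragraph below Table 3 and in the Discussion. If the rise in year 2 is real, say so and give the reason in place of the appeal to 0-44%.

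The cost is a recalculation and some rewritten text. No extra patients are needed. The stated power will probably be less favourable: about 80-81% once crossover is included even if the rates are truly annual, and lower if they are cumulative.
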